#### Additional analyses

Safety analysis: general safety evaluations will be based on the incidence and type of AEs. Safety variables will be tabulated and presented for all the patients in safety sets. AEs will be coded using the tools proposed by the World Society of Intravenous Anesthesia International Sedation Task Force. The number (%) of subjects with any AEs will be summarized and compared via *χ*^2^ test, continuity correction *χ*^2^ test, or Fisher’s exact test.

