**Step 2: Please DESCRIBE the adverse event(s). Check all that apply.**				
**Minimal risk descriptors**	**Minor risk descriptors**		**Sentinel risk descriptors**	
□ Vomiting/retching	□ Oxygen desaturation (75–90%) for < 60s		□ Oxygen desaturation, severe (<75% at any time) or prolonged (<90% for >60s)	Other, specify below
□ Sub-clinical respiratory depression^a^	□ Apnoea not prolonged		□ Apnoea, prolonged (>60s)	
□ Muscle rigidity, Myoclonus	□ Airway obstruction		□ Cardiovascular collapse/shock^g^	
□ Hypersalivation	□ Failed sedation^e^		□ Cardiac arrest/absent pulse	
□ Paradoxical response^b^	□ Allergic reaction without anaphylaxis			
□ Recovery agitation^c^	□ Bradycardiat^f^			
□ Prolonged recovery^d^	□ Tachycardia^f^			
	□ Hypotension^f^			
	□ Hypertension^f^			
	□ Seizure			

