**Step 5: Assign a SEVERITY rating to the adverse event(s) associated with this sedation encounter.**				
If there are any options checked in the Sentinel columns above, then this is a Sentinel adverse event^j^.				
If the most serious option(s) checked above are Moderate risk, then this is a Moderate risk adverse event^k^.				
If the most serious option(s) checked above are Minor risk, then this is a Minor risk adverse event^l^.				
If the most serious option(s) checked above are Minimal risk, then this is a Minimal risk adverse event^m^.				

Footnotes:

^a^ “Sub-clinical respiratory depression” is defined as capnographic abnormalities suggesting respiratory depression that do not manifest clinically

^b^ “Paradoxical response” is defined as unanticipated restlessness or agitation in response to sedatives

^c^ “Recovery agitation” is defined as abnormal patient affect or behaviors during the recovery phase that can include crying, agitation, delirium, dysphoria, hallucinations, or nightmares

^d^ “Prolonged recovery” is defined as failure to return to baseline clinical status within 2 hours

^e^ “Failed sedation” is defined as inability to attain suitable conditions to humanely perform the procedure

^f^ Alteration in vitals signs (bradycardia, tachycardia, hypotension, hypertension) is defined as a change of >25% from baseline

^g^ “Cardiovascular collapse/shock” is defined as clinical evidence of inadequate perfusion

^h^ Examples of “escalation of care” include transfer from ward to intensive care, and prolonged hospitalization

^i^ “Pulmonary aspiration syndrome” is defined as known or suspected inhalation of foreign material such as gastric contents into the respiratory tract associated with new or worsening respiratory signs

^j^ “Sentinel” adverse events are those critical enough to represent real or serious imminent risk of serious and major patient injury. Once recognized, they warrant immediate and aggressive rescue interventions. Once clinically concluded, they warrant immediate reporting within sedation care systems and the highest level of peer scrutiny for continuous quality improvement

^k^ “Moderate” adverse events are those that, while not sentinel, are serious enough to quickly endanger the patient if not promptly managed. Once clinically concluded, they warrant timely reporting within sedation care systems and periodic peer scrutiny for continuous quality improvement

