### Outcomes {12}

#### Primary outcome measures

The primary outcome of this study is the incidence of hypoxia (75% ≤ SpO_2_ < 90% for <60 s) in the two groups from the beginning to the end of the operation.

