#### Secondary outcome measures

The secondary outcomes comprise the following:The incidence of subclinical respiratory depression (90% ≤ SpO_2_ < 95%) in the two groups from the beginning to the end of the operation.The incidence of severe hypoxia (SpO_2_ < 75% or 75% ≤ SpO_2_ < 90% for ≥60 s) in the two groups from the beginning to the end of the operation.The incidence of other AEs recorded via tools proposed by the World Society of Intravenous Anesthesia International Sedation Task Force.

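### The between-arm test of any adverse event uses a form that includes the primary and severe hypoxia outcomes, although the outcome is defined as other AEs

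*Protocol article*

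**What the plan says.** The safety paragraph under Additional analyses says that "general safety evaluations will be based on the incidence and type of AEs" and that "AEs will be coded using the tools proposed by the World Society of Intravenous Anesthesia International Sedation Task Force". It then names one between-arm comparison: "The number (%) of subjects with any AEs will be summarized and compared via" a chi-square, continuity-corrected chi-square or Fisher's exact test.

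The tool is reproduced as Table 2. Step 2 lists, among the adverse events to be ticked:
- a minor-risk item, "Oxygen desaturation (75–90%) for < 60s"
- a sentinel-risk item, "Oxygen desaturation, severe (<75% at any time) or prolonged (<90% for >60s)"
- a minimal-risk item, sub-clinical respiratory depression, which footnote a says "is defined as capnographic abnormalities suggesting respiratory depression that do not manifest clinically"

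Under Outcomes, "The primary outcome of this study is the incidence of hypoxia", with SpO2 from 75% to below 90% for less than 60 s. The secondary outcomes are subclinical respiratory depression (SpO2 from 90% to below 95%), severe hypoxia (below 75%, or 75% to below 90% for at least 60 s), and "The incidence of other AEs recorded via tools proposed by the World Society of Intravenous Anesthesia International Sedation Task Force". The Objectives use the same word, other. Table 3 gives adverse events a row of their own, apart from the three hypoxia rows.

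**The concern.** The outcome is defined as AEs other than the hypoxia outcomes. The analysis is written for any AE on a form that contains two of those outcomes, and nothing in the safety paragraph removes them. Followed literally, the only between-arm safety test that the paragraph names is partly a second test of efficacy. Two things are at stake:

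- A hypoxia benefit with no other change lowers the any-AE rate and could be reported as a separate safety finding.
- A real excess of other events in the capnography arm could be offset in the total by the hypoxia events avoided.

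A separate problem concerns the sub-clinical item. It shares a name with a secondary outcome but is a different event, defined by capnographic abnormality. According to the Intervention description, capnographic data are not visible in the control arm. The item can therefore be ticked readily in one arm only, which would inflate AE counts there.

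**Working it through.** **Inputs from the protocol (Sample size).** Hypoxia 8% in control and 4% with capnography; two-sided alpha 5%; power 90%; 1:1 allocation; 10% dropout; about 1800 patients. That gives 900 per arm randomised and 900 × 0.9 = 810 per arm after dropout.

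**Check of the protocol's own figure.** The continuity-corrected two-proportion formula gives 788 per arm; 788/0.9 rounds up to 876, or 1752 in total, within 3% of 1800. Without the correction it is 739 per arm and 1644 in total. The stated size is reproduced with the continuity correction.

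**Assumptions not in the documents.** The rate of other AEs (5%, 10% or 20%) and its independence from hypoxia. The sub-clinical item is left out of these calculations.

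**Spill-over, with other AEs equal in both arms.** Any-AE rate = 1 − (1 − hypoxia)(1 − other).

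At other = 10%:
- control: 1 − 0.92 × 0.90 = 17.2%
- capnography: 1 − 0.96 × 0.90 = 13.6%
- pooled rate 15.4%; standard error = √(2 × 0.154 × 0.846/810) = 0.01794
- z = 0.036/0.01794 = 2.01, p about 0.045
- with continuity correction, z = (0.036 − 1/810)/0.01794 = 1.94, p about 0.053

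| Other AEs (assumed) | Any AE, control vs capnography | p at expected counts, uncorrected, 810 per arm | Chance of a significant difference, 810 / 900 per arm |
|---|---|---|---|
| 5% | 12.6% vs 8.8% | 0.013 | 70% / 74% |
| 10% | 17.2% vs 13.6% | 0.045 | 52% / 56% |
| 20% | 26.4% vs 23.2% | 0.14 | 32% / 35% |

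With hypoxia excluded and no true difference in other AEs, the chance of a significant result in favour of capnography would be the nominal 2.5%.

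**Sensitivity to overlap.** If no patient has both hypoxia and another AE, the chances at 900 per arm rise to 77%, 64% and 49%. If every hypoxic patient also has another AE, the any-AE rate equals the other-AE rate in each arm and the spill-over is zero.

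**Offset.** The other-AE rate in the capnography arm that makes the any-AE totals equal is 1 − (1 − control any-AE rate)/0.96. With 10% in control: 1 − 0.828/0.96 = 13.75%. That is 0.0375 × 810 = about 30 extra patients, with 17.2% any AE in both arms. Tested alone, 13.75% against 10% gives z = 2.33, p about 0.02, with power of about 65% at 810 per arm.

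**The case against.** The best defence is that the separation is already in the document. The Objectives and secondary outcomes say other AEs, Table 3 lists adverse events apart from hypoxia, and the hypoxia tests come before the safety paragraph. That paragraph can therefore be read as the analysis of other AEs. This is a fair reading, but it is not what the paragraph says. It names any AEs and points to a tool on which desaturation is an AE. The two places conflict, so this is more than detail left to a fuller document.

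A second defence is that hypoxia is an adverse event, that the abstract calls it one, and that an all-inclusive count is a legitimate measure of net harm. That stands. A reader might infer that no test of such a total is acceptable. The documents do not support that; what matters is that the total is labelled for what it contains.

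Third, safety is also evaluated by type of AE. This stands too. A reader might infer that an excess of other harms would go unseen, but the tabulation could still show it. Only the tested total is affected.

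Fourth, the size rests on assumptions. Apnoea and airway obstruction are also on the form, and the Discussion names hypoventilation as the primary cause of hypoxia, so positive overlap is plausible and would shrink the spill-over. At 20% other AEs the difference is not significant at expected counts, and at 10% significance depends on which of the listed tests is used.

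**Conclusion.** The point holds as an inconsistency between the outcome definition and the stated test. Two of the form's items, the brief and the severe or prolonged desaturation items, are in substance the primary outcome and the severe-hypoxia secondary outcome. Under the protocol's 8% to 4% assumption they alone could produce an apparent safety benefit: 17.2% against 13.6% at an assumed 10% of independent other AEs. They could also offset a rise in other AEs to 13.75%. Both figures depend on a rate and a degree of overlap that the documents do not give.

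Two stronger readings are not supported. One is that all three respiratory items on the form duplicate trial outcomes. The sub-clinical item is capnographic and the secondary outcome is an SpO2 range, so they share only a name. The other is that the any-AE test must favour capnography, so that correcting it would make the contrast less favourable to that arm. Because the sub-clinical item can be observed only in the open arm, it can raise the count there, and the net direction is unknown.

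The primary analysis is untouched. The change is still worth making, because the any-AE result as written cannot be read as safety evidence independent of efficacy.

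**What to change.** In the safety paragraph, define the compared endpoint as subjects with at least one AE other than the two desaturation items and the capnography-defined sub-clinical item, to match other AEs in the secondary outcomes. Tabulate those three items by arm in separate rows, and note that the sub-clinical item depends on a readout not visible in the control arm. If an all-inclusive total is also reported, label it as including the efficacy outcomes and do not present it as independent safety evidence.

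The cost is about one sentence. No new data are needed, because the form records each item separately. The drawback is that the tested safety count covers fewer events.

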### Interim analyzes {21b}

Not applicable as we have no plans to conduct any interim analyses, and no one has the rights to access these interim results and decide to terminate the trial.

### Methods for additional analyses (e.g., subgroup analyses) {20b}

The association between the baseline characteristics and intervention and the risk of total hypoxia cumulative incidence was examined using univariable- and multivariable-adjusted logistic regression models. The results were presented as the odds ratios and corresponding 95% confidence intervals.

### Methods in the analysis to handle protocol nonadherence and any statistical methods to handle missing data {20c}

Statistical analysis was performed based on intention-to-treat. Regardless of protocol adherence, the results of the outcome analyses will be randomly analyzed. The frequency and type of missingness of all the variables will be screened. If missingness is >5% of any variable, we will use multiple imputations. Complete case analysis will be performed as a sensitivity analysis, in case of missing data and imputation.

### Plans to provide access to the full protocol, participant-level data, and statistical code {31c}

Not applicable as we have no plans to provide access to the full protocol, participant-level data, and statistical code.

### Composition of the data monitoring committee, its role, and reporting structure {21a}

We do not have composition of the data monitoring committee (DMC).

### Adverse event reporting and harms {22}

The nasal cannula with a port that is used for collecting exhaled CO_2_ samples, which are consequently used for capnographic monitoring, is similar to the original nasal cannula and does not have any additional risks. To date, to the best of our knowledge, there has been no evidence that this study may cause any risk or discomfort to the participants.

We will record any AEs that occur during the clinical trial, regardless of whether these events were associated with the intervention. Additionally, all the expected and unexpected trial-related AEs will be reported in the trial publications.

### Frequency and plans for auditing trial conduct {23}

The investigators shall maintain all study data according to GCP requirements. The original study data and information will be retained for at least 5 years following trial completion. Data security and monitoring reports will be submitted to the ethical committee every 3 months.

### Plans for communicating important protocol amendments to relevant parties (e.g., trial participants, ethical committees) {25}

This clinical trial will be conducted according to the ethical committee approval. Any problem or protocol modifications during the trial will be communicated to the ethical committees, trial participants, trial registries, journals, and regulators in a timely manner. The ethical committee’s consent will be required to change the protocol.

### Dissemination plans {31a}

The participants, healthcare professionals, the public, and other relevant groups in the form of articles will communicate the results of this trial.

## Discussion

This study is the first randomized controlled trial designed to confirm the utility of capnographic monitoring in older patients during gastrointestinal endoscopy under sedation. The proportion of older patients who undergo gastrointestinal endoscopy under sedation is increasing annually worldwide. Ensuring the safety of older patients during gastrointestinal endoscopy under sedation is thus crucial.

Hypoxia is the most common and severe complication that occurs during gastrointestinal endoscopy under sedation, with the primary cause of hypoxia being hypoventilation due to propofol administration. Older patients are more susceptible to respiratory depression and hypoxia than adult patients [12, 13].

The early detection of respiratory depression in patients and timely and effective intervention measures can reduce the occurrence of severe hypoxia, hypercapnia, and even cardiac arrest, thereby improving patient prognosis [14]. Capnography monitoring is more sensitive and real-time than SpO2 in reflecting respiratory depression before the onset of hypoxia [15–17].

Currently, no unified conclusion has been drawn on whether end-tidal CO2 monitoring can effectively reduce the occurrence of hypoxia during endoscopy [18–23]. There is insufficient evidence for routine capnographic monitoring in all patients during sedated gastrointestinal endoscopy, and there have been few recent studies to add to the scant literature on this topic. Our study design avoids some of the limitations of the other studies and demonstrates more closeness to clinical settings. Our study is expected to provide a higher level of evidence and improve the safety of gastrointestinal endoscopy under sedation in older patients.

Therefore, future research should seek to resolve some of the limitations of this study. First, this was a single-blinded clinical study, which might cause potential bias. Second, our trial is not international, and the participating institutions of our experiment are all Grade III Class A general hospitals in China. The medications or methods of sedation vary among different institutions and countries. Fortunately, the selected intravenous anesthetics are widely used owing to their clinical compatibility, and the data obtained in our study could be represented in most clinical settings. Third, only older patients with ASA grades I–II were included in our trial, and those with ASA grades III–IV were excluded. We planned another group to be explored in the next study for older patients with higher ASA classifications. Therefore, further capnography monitoring research in gastrointestinal endoscopy under sedation is warranted.

## Trial status

Trial registration: ClinicalTrials.gov, NCT05030870. Registered on September 1, 2021. The protocol version is 2.2, which was approved in November 22, 2021. This study was started on September 1, 2021, and the recruitment phase will last until December 2023.

## Data Availability

Because of Chinese data protection rules and regulations, the participant-level data set cannot be made publicly available. If requested, the statistical code is available.

## Abbreviations

SpO_2_: Hemoglobin oxygen saturation
CRF: Case report form
GCP: Good clinical practice
REC: Research Ethics Committee
FAS: Full analysis set
PPS: Per-protocol set
SAS: Safety analysis set
AEs: Adverse events
ITT: Intention-to-treat
DMC: Data monitoring committee
CO_2_: Carbon dioxide
RCT: Randomized controlled study
